**|Visit two**

1. The main research will check the laboratory results of tests. The results will be noted in the clinical evaluation and laboratory records. In the case of laboratory abnormalities that contraindicate the MTX, the patient will be excluded. The result of fasting blood glucose will be reassessed to verify if it meets the criteria for diabetes.
2. The physical examination will be performed to reassess the severity of psoriasis by the PASI score with the methodology described previously.
3. The blood collection and TST application will be performed by *[name]* using the Mantoux technique. The samples will be identified with the inscription “Sample 2”, date, hour, and research number.
4. The sample will be delivered to forwarded to the respective laboratories immediately after collection, will be centrifuged, and incubated in a maximum of 1 hour. The samples from visits 1 and 2 will be stored in different trays after freezing.

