- Verify the association between the sustainer status with sex, age categorized, disease duration, weight, BMI, alcohol consumption, smoking, presence of other forms of psoriasis associated, blood glucose (normal, diabetic), serum levels of INF-γ, TNF-α, interleukin-12, interleukin-17, interleukin-23, ESR, CPR. The association with ESR, CPR, and cytokines will be verified before and after treatment. The variables presenting p < 0.05 will be considered a positive association.

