#### Methods of collection

#### Collection protocol

**Evaluation visit**

Patients who meet the inclusion criteria will be invited to participate in the research. The patient will only initiate the research protocol after signing the “Free and Informed Consent Term” (Appendix 1). After signing the consent form, the main researcher will collect the demographic data by interview and identification document. The data will include the date of birth, current age, comorbidities, and current medications in use (Appendix 2).

Next, the presence of the BCG vaccine scar will be checked. In the absence of the scar, the patient will be excluded. In the presence of BCG vaccine scar, other exclusion criteria will be verified; current or less than six months use of topical treatment for psoriasis and current or previous systemic treatment for psoriasis (Appendix 2). A standardized questionnaire will be used to assess the presence of active TB (Appendix 3) In the case of a positive response to any active TB symptom, history of TB treatment, or history of TB prophylaxis the patient will be excluded.

After the interview, the patients will be scheduled for collection of exams in the laboratory of the hospital of the UFPE clinics tree days before the visit one. These will include complete blood count, liver enzymes, renal function, serology of hepatitis B, C, HIV, erythrocyte sedimentation rate, quantitative C- reactive protein, rheumatoid factor, and pregnancy test for women. The chest X-ray will be performed in the radiology department of the hospital.

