**Visit one**

The first visit will be done following the following protocol:

1. The main research will check the laboratory results of tests and the chest *x*-ray report. The results will be noted on the Clinical Data Record (Appendix 2) and in Laboratory follow-up Record (Appendix 4). In the case of contraindications to MTX or pulmonary radiological changes not due to possible LTBI, the patient will be excluded. The result of fasting blood glucose will be noted in mg/dl (Appendix 4).
2. The physical examination will be performed by the main research to check the severity and associated forms of psoriasis. It will be verified the presence of geographic tongue, nail psoriasis, inverted psoriasis, palm-plantar psoriasis, and scalp psoriasis. The severity of psoriasis will be quantified by the PASI score (Appendix 5)
3. The laboratory tests will be realized by *[name]*. The blood will be obtained by direct venipuncture in appropriate tubes. For the QuantiFERON-TB Gold test, one milliliter of blood will be collected in each of three tubes separately according to the sequence in the manufacturer's instructions (Cellestis, Melbourne, Australia). For the IFN-γ and TNF-α tests, 3 ml of blood will be collected in a tube with citrate. The blood samples will be identified with the inscription “Sample 1”, date, hour, and research number.
4. The blood samples will be immediately forwarded to the respective laboratories by the main research in a Styrofoam box. First, the samples for cytokines will be sent to the Laboratory of Immunopathology Keizo Asami-LIKA under the responsibility of [name]. Second, the IGRA will be sent to the laboratory of Immunoepidemiology, Department of Immunology, Aggeu Magalhães Research Center (CPqAM) -Fiocruz under the responsibility of [name].
5. After the collection of blood, TST will be performed by *[name]* using the Mantoux technique described above.

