**Follow up period**

1. The patient will be scheduled every three months to check the PASI and the laboratory results: Complete blood count, liver enzymes, renal function, CPR, ESR, and pregnancy test for women. Fast blood glycemia and cholesterol will be requested according to the need of each patient.
2. The follow-up period of the study will end in February 2018. However, the patients will be kept on follow-up at the outpatient clinic for an indeterminate period, unless they abandon follow-up.
3. In case of loss of PASI response to below 50%, patients will have their medication modified according to each case by main research.

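### PASI is scored after the laboratory check with ESR and CRP not withheld, so observer bias is possible when PASI-defined sustainer status is tested against those two markers

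*Protocol*

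**What the plan says.** The relevant statements are spread over several sections of the protocol.

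- **Evaluation visit (4.1).** The blood panel is scheduled "tree days before the visit one" and includes "erythrocyte sedimentation rate, quantitative C- reactive protein, rheumatoid factor, and pregnancy test for women".
- **Visit one (4.1).** Item 1: "The main research will check the laboratory results of tests and the chest *x*-ray report". The results go onto the Appendix 2 and Appendix 4 records, and Appendix 4 has rows for ESR and CRP. Item 2: "The physical examination will be performed by the main research to check the severity and associated forms of psoriasis". PASI is scored in that examination.
- **TST reading visit one (4.1), item 4.** ESR and CRP are repeated at three months, in the work scheduled before visit two.
- **Visit two (4.1).** Item 1: "The main research will check the laboratory results of tests". Item 2 is the examination with PASI. It refers back to the earlier method and does not name the scorer.
- **Follow up period (4.1).** "The patient will be scheduled every three months to check the PASI and the laboratory results", with CRP and ESR in the list.
- **Variables definition (4.2).** A sustainer has a PASI reduction of at least 50% at 12 weeks, kept to the end of follow-up.
- **Secondary objectives and Data analysis plan.** Sustainer status is tested against continuous variables by t-test or Mann-Whitney at p < 0.05. "The association with ESR, CPR, and cytokines will be verified before and after treatment".

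No section provides a masked or second PASI scorer, or has PASI closed before results are read.

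**The concern.** PASI rests on the researcher's estimate of the area involved and a by-eye grading of erythema, infiltration and flaking. A scorer who has just seen a raised or normalised CRP may grade slightly differently without intending to. That score feeds the 50% cut, and the resulting class is then compared on the same CRP and ESR. An association created by scoring would look the same as a real relation between inflammation and response, and no later analysis could separate the two.

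Treatment cannot be masked in a single-arm study, but knowledge of two laboratory values can be limited. The protocol already does this in effect for the cytokines: section 4.3.2 defers their ELISA until inclusion has ended, so most PASI scores are made without them. ESR and CRP enter the same analysis without that protection.

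**Working it through.** **1. Is the chain in the text?**

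- *ESR and CRP available at scoring.* They are in the panel before visit one and in the three-month panel before visit two. Appendix 4, where visit-one results are noted, has rows for both. The visit items themselves speak only of laboratory results, so it is an inference, though a close one, that these two values are among those read.
- *Order.* Item 1 (laboratory) precedes item 2 (PASI) at both visits. The follow-up section lists both and fixes no order.
- *Same person.* This is explicit at visit one. At visit two it is implied, since no other PASI scorer appears.
- *Link to the analysis.* PASI gives sustainer status, which is tested against ESR and CRP, each before and after treatment: 2 × 2 = 4 comparisons.

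**2. The plan's own figure.** The protocol gives 22 pairs for effect size 0.65, 80% power, 5% two-sided.

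- Normal formula: ((1.960 + 0.842)/0.65)² = 18.6. Adding 1.960²/2 = 1.9 gives 20.5, so 21.
- Exact noncentral t: 21 pairs give 80.9% power and 22 give 82.8%.
- Dividing 21 by the Wilcoxon efficiency 0.955 gives 21.99, so 22.

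The figure is consistent. It serves below only as the number of patients; the point does not depend on it.

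**3. Which way would a nudge act?** Sustainer status uses percentage reduction, so the two visits work in opposite directions. Invented scores, with a 5% nudge:

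- 12 to 6 is a 50% reduction. If only the second score is raised, 12 to 6.3 gives (12 − 6.3)/12 = 47.5%, and the patient drops below the cut.
- 12 to 6.2 is 48.3%. If only the first score is raised, 12.6 to 6.2 gives (12.6 − 6.2)/12.6 = 50.8%, and the patient rises above it.
- If both scores are raised in proportion, 12.6 to 6.3 is again 50%, and nothing changes.

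The net direction is therefore not known.

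**4. How many patients lie near the cut?** The protocol gives no distribution for PASI reduction. Assuming normality, the share between 45% and 55% is:

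- mean 50, SD 30: 0.132, or 2.9 of 22
- mean 50, SD 20: 0.197, or 4.3 of 22
- mean 60, SD 30: 0.125, or 2.8 of 22

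**5. What a net shift would do.** This simulation uses 22 patients, mean reduction 50%, SD 20 or 30 points, no true association, and a t-test at 5%. Scored reduction equals true reduction minus b points per SD of the marker (6,000 runs per cell).

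| b (points per SD) | False positives, SD 20 | False positives, SD 30 |
|---|---|---|
| 0 | 5% | 5% |
| 2.5 | 7% | 6% |
| 5 | 14% | 9% |
| 10 | 38% | 21% |

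Every input except the 22 and the 5% is an assumption. The model takes a shift that does not cancel between visits, and it classifies on the 12-week reduction alone.

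**The case against.** Reading eligibility and safety results before examining the patient is a workable order, because item 1 can lead to exclusion. The protocol makes no claim of masked assessment that this order would contradict. The analysis at stake is one part of a secondary objective, and the cytokines in it are largely unaffected. All of this stands and keeps the point small.

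The following readings are tempting but unsupported:

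- *That the researcher reads ESR and CRP immediately before every PASI.* The visit items do not name the markers, visit two does not name the scorer, and the follow-up section sets no order.
- *That sustainer status is in fact dependent on the markers through scoring.* The protocol allows this; nothing in it shows that it happens, and step 3 shows that nudges at the two visits can offset each other.
- *That a 2 × 2 Fisher table shows the effect.* The plan's Fisher list omits ESR and CRP, which are tested as continuous variables.
- *That swapping items 1 and 2 removes the problem.* Appendix 4 is one cumulative sheet. Baseline values would still be known at visit two, and 12-week values at follow-up, where maintenance of response is decided.

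The objection does not dispose of the core. The order of assessment is a stated procedure, the scorer is not masked, and the protection costs almost nothing.

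**Conclusion.** The point holds as a cheap improvement. Four secondary comparisons, sustainer status against ESR and CRP before and after treatment, are open to observer bias because PASI follows a laboratory check whose panels include those markers. The size and direction of any bias are unknown. The simulated rates in the working show only what an assumed net shift would do in 22 patients, and are not estimates for this trial. The conclusion rests on two inferences: that ESR and CRP are among the results checked, and that the same researcher scores PASI at visit two. It does not show that the sustainer results would be wrong.

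**What to change.** 1. At visits one and two and at each three-monthly check, complete and sign the Appendix 5 PASI form before that visit's ESR and CRP results are opened.
2. Keep ESR and CRP off the Appendix 4 sheet used by the PASI scorer. Record them separately, for example on Appendix 6, which already has rows for both, and open that record only after the PASI form is signed, ideally after the last PASI used for sustainer status. Appendix 6 has only before and after columns, which is enough for the planned tests; three-monthly values need their own sheet. It gives CRP in mg/dl while section 4.2 uses mg/l, so the units should be aligned.
3. State who scores PASI at visit two and at follow-up.

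The other laboratory and eligibility checks can stay where they are; neither marker is among the exclusion criteria listed in section 3.3.

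The cost is a small change in record handling. If PASI is instead moved ahead of the whole laboratory check, add a few minutes of scoring in patients then excluded. Where ESR or CRP must be seen for clinical reasons, some bias remains possible, and the report should say so.

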**TST reading visit two**

1. The patient will be scheduled to read the result of the TST in 72 hours. The TST reading will be performed by *[name]* as the same as visit 1.

**Follow up period**

1. The patient will be scheduled every three months to check the PASI and the laboratory results: Complete blood count, liver enzymes, renal function, CPR, ESR, and pregnancy test for women. Fast blood glycemia and cholesterol will be requested according to the need of each patient.
2. The follow-up period of the study will end in February 2018. However, the patients will be kept on follow-up at the outpatient clinic for an indeterminate period, unless they abandon follow-up.
3. In case of loss of PASI response to below 50%, patients will have their medication modified according to each case by main research.

4.2 Variables definition

| Variable | Definition | Categorization |
| --- | --- | --- |
| ***TB screening*** | |  |
| **Quantiferon TB- gold first categorization** | Tests classified as positive by the manufacturer | 1. Positive |
|  | Tests classified as positive by the manufacturer | 1. Indeterminate |
|  | Tests classified as positive by the manufacturer | 1. Negative |
| **QuantiFERON TB-gold second categorization** | Tests classified as positive or undetermined | 1. Positive |
|  | Tests classified as negative | 1. Negative |
| **TST first categorization** | <5 mm | 1. Negative |
|  | 5 mm ≤ TST < 10 mm | 1. Indeterminate |
|  | ≥ 10 mm | 1. Positive |
| **TST second categorization** | <5 mm | 1. Negative |
|  | ≥ 5 mm | 1. Positive |

| *Cytokines* | |  |
| --- | --- | --- |
| **TNF-α** | in pg/ml | Average |
| **IFN-γ** | in pg/ml | Average |
| **IL -12** | in pg/ml | Average |
| **IL- 17** | in pg/ml | Average |
| **IL-23** | in pg/ml | Average |
| ***Inflammatory markers*** | |  |
| **CRP** | in mg/l | 1. ≤ 1 2. > 1 |
|  |  | Average |
| **ESR** | in mm/h | 1. ≤10 2. >10 |
|  |  | Average |
| ***Clinic*** |  |  |
| **PASI absolute** | psoriasis severity index calculated as described in methods | Mean/median |
| **PASI reduction** | Percentage reduction of PASI after the use of methotrexate | 1. <50% 2. 51-74% 3. > 75 %   Média/mediana |

| Variable | Definition | Method | Categorization |
| --- | --- | --- | --- |
| Sex | Biological gender of the patient | Interview | 1. Male 2. Female |
| Age | The time between the date of birth and study interview day, in full years | Identification document | 1. *18 ≥ x* < *30* 2. *30 ≥ x < 60* 3. *≥ 60*   Average |
| Disease duration | Estimated time between the age of onset of illness and the age at study interview day in full years | Interview | 1. < 2 year 2. 2 *≥ x <* 10 years 3. *≥ 10*  years   Average |
| alcohol intake | Have consumed more than one dose per day if the patient is a woman or 2 doses if is a man in the last 30 days. | Interview | 1. Yes 2. No |
| Smoking | I have smoked for more than one day in the last 30 days. | Interview | 1. Yes 2. No |
| Contact with Tb carrier | Characterized by a family history of TB (parents, uncles, grandparents, partners, children or own patient), know someone with TB as a neighbor, friends, co-workers or works in a high-risk TB environment | standardized questionnaire | 1. Yes 2. No |
| Place of residence | Urbanization of the place of residence | Interview | 1. Urban zone 2. Rural area |
| Contact with cattle | A person who has worked or had contact for a long time with cattle | Interview | 1. Yes 2. No |
| Nail psoriasis | Presence of pits, onycholysis, splinter hemorrhages, and hyperkeratosis not attributed to another cause in at least one nail. | Physical exam | 1. Yes 2. No |
| Geographical language | Smooth red spots on the tongue | Physical exam | 1. Yes 2. No |
| Psoriasis Scalp | Presence of psoriasis plaques on the scalp | Physical exam | 1. Yes 2. No |
| Palmoplantar psoriasis | Presence of psoriasis plaques on the palms or plants may transgress to the back | Physical exam | 1. Yes 2. No |
| Inverted psoriasis | Presence of psoriasis plaques fold areas | Physical exam | 1. Yes 2. No |
| Enthesitis | Patient presents pain on palpation of entheses without signs of arthritis | Physical exam | 1. Yes 2. No |
| Diabetes | Use of medication for diabetes or two fasting blood glucose levels above 126 mg/dl or an aleatory blood glucose level above 200 mg/dl. | Interview Laboratory tests | 1. Yes 2. No |
| Blood glucose | in mg/ml. | Laboratory tests | average |
| Chest X-ray suggestive of LTBI | Presence of retraction, calcification, hilar or mediastinal lymph node enlargement, or pleural alterations. | Image examination | 1. Yes 2. No |

| Variable | Definition | Method | Categorization |
| --- | --- | --- | --- |
| Treatment maintenance | Defined as patients who achieved 50% or more reduction in PASI score after 12 weeks of treatment and maintained this reduction until the end of the follow-up period. | Physical exam | Sustainer |
|  | Defined as patients who did not achieve a 50% reduction in PASI or those who did but lost response over the follow-up period and need a change in medication. | Physical exam | Non-sustainer |

- 1. Collection techniques
     1. **PASI**

The PASI will be carried out according to the methodology described below:

1) Each body area (head, trunk, upper limbs and lower limbs) will have their percentage of involvement determined by the researcher and will receive a number according the percentage of committed area: 1 < 10%; 2 = 10-29%; 3 = 30-49%; 4 = 50-69%; 5 = 70-89% and 6 = 90-100%

2) Each characteristic of the psoriasis plates (erythema, infiltration and flaking) will be classified at: 0 = absent, 1 = mild, 2 = moderate, and 3 = severe. The values assigned to the characteristics will be summed up for that area.

3) The value obtained in 1 will be multiplied by the value obtained in 2 for each area.

4) The product of this equation will be multiplied by a constant that depicts the proportionality of the area of each body follow-up. The head = 0.1; The trunk = 0.3; The upper limbs = 0.2 and the lower members = 0.4.

5) After the following calculation, the values will be summed up, resulting in an absolute number reflects the severity of psoriasis.

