#### 3.1 Study period

| *Phase/year* | ***2014*** | ***2015*** | ***2016*** | ***2017*** | ***2018*** |
| --- | --- | --- | --- | --- | --- |
| Scientific project | X |  |  |  |  |
| Ethics committee submission |  | X |  |  |  |
| Data collection and follow up* |  | X** | X | X | X |
| Laboratory analysis |  |  |  | X |  |
| Data analysis |  |  |  | X | X |
| Manufacture of scientific articles |  |  |  |  | X |

* The deadline for the final analysis of data from the follow-up period will be February 2018.

* * The Collection can only be initiated after approval by the ethics committee.

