3.2 Sampling type and sample size definition

The sample will be systematic random.

It will be included sequentially patients over 18 years of age with moderate to severe plaque psoriasis with the indication of methotrexate referred by dermatologists to initiate the follow-up in the outpatient clinics of the Hospital of the Federal University of Pernambuco who meet the eligibility criteria and sign the consent form.

The sample size calculation was performed considering the effect of MTX on PASI. The calculation used the formula for comparing paired differences.

To achieve a power of 80 % and a level of significance of 5 % (two-sided) for detecting an effect size of 0,65 between pair was necessary 22 pairs.

For the other variables, the objective was to verify if this effect produced on the PASI would be sufficient to produce a change in them.

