**4.3.3 QuantiFERON TB Gold In-Tube test**

The QuantiFERON TB Gold In-Tube test (QFT-GIT) (Cellestis, Melbourne, Vic. Australia) will be performed according to the standards described by the manufacturer

1. Collection of material: Blood samples will be obtained before the execution of TT using a vacutainer-type needle in specific collection tubes. One milliliter of blood will be collected from each participant in each tube separately following the sequence: gray-antigen-free tube (null control), red tube-TB antigen (ESAT-6, CPF-10, TB7.7) and purple tube-with hemagglutinin (mitogen or positive control). The tubes will be shared 10 times to contact the blood with the antigens.
2. Sample processing: Samples were incubated within a period of up to 1 hour after collection of blood. The tubes will be gently homogenized by inversion and taken to the oven at 37 ° C and placed vertically for 16 to 24 hours for incubation.
3. After incubation, the tubes will be centrifuged for 15 minutes between 2000 and 3000 RPM for plasma separation. The removed plasma will be placed in cryotubes and then frozen at minus 70 ° for further performance of the second phase of the technique. The cryotubes will be stored with the same identification made on the collection in separately identified trays (SAMPLE 1, SAMPLE 2).
4. The Elisa will be held only after the end of the inclusion period. The exams will be carried out in duplicate.

The regents except the 100X conjugate concentrate will be placed at room temperature for 60 minutes (min). During this time, the standard concentration was 8.0 IU / ml, and the conjugate 100X concentrated, both in distilled water. After reconstitution, the standard will be diluted using the diluent available in the kit: 4 IU / ml, 1UI / ml, 0.25 IU / ml, 0 IU / ml (in the latter, only green diluent).

After the dilutions were performed, 50μL of conjugate will be distributed in each well of the microtiter plate, then 50μL of plasma from the first test step was added to each well. This mixture was stirred for 1 min on a microplate shaker. At the end of this process, the plate containing the samples was covered to avoid exposure to light and incubated for 120 min at room temperature.

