#### Data analysis plan

The IBM Statistical Package version 23.0 (IBM corp., Armonk, NY) will be used for the statistical calculations.

- Data will be analyzed descriptively through statistical measures: mean ± standard deviation or median and percentiles for numerical variables and absolute and percentage frequencies for categorical variables.
- It will be verified whether there is a significant change in the results of TST and/or IGRA tests, with 2 or 3 categories, classified according to the variables descriptions by the McNemar test. A P < 0,05 will be considered significant.
- It will be verified whether the difference in the comparison of test results is significant before and/ or after treatment by the McNemar test. A P < 0,05 will be considered significant.
- The agreement between each and between the IGRA and the TST before and after treatment, with two or three categories, will be verified by the Cohen’s kappa.
- For numeric continuous variables, the normality will be tested using the Shapiro-Wilk test. To compare the mean of paired continuous variables will be used the Student's t-test for paired variables for variables with a normal distribution, and the Wilcoxon test for variables with a non-normal distribution.
- To compare the TST and IGRA results with the means of numerical continuous variables will be used the Student's t-test for variables with a normal distribution, and the Mann-Whitney test for variables with a non-normal distribution.
- Will be verified the association between the sustainers or non-sustainers status with the categorized variables by the Fisher Exact test. The variables presenting p < 0.05 will be considered a positive association. The variables will be sex, age categorized, duration of illness categorized, alcohol consumption, smoking, presence of other forms of psoriasis associated, blood glucose (normal, diabetic).
- The association between the sustainers or non-sustainers status with the medians/medians of the continuous variables will be verified by t-Student test or Mann-Whitney test, The variables will be the age in years, disease duration in years, BMI, blood glucose in mg/dl, serum levels of INF-γ, TNF-α, interleukin-12, interleukin-17, interleukin-23, ESR, CPR. The association with ESR, CPR, and cytokines will be verified before and after treatment.
- The variables presenting p < 0.05 will be considered a positive association.

.

1. ***Budget****

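### Sustainer status has no common time horizon: week-12 responders who enter late have less time to lose response, and the planned tests ignore this

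*Protocol*

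**What the plan says.** Section 4.2 (Treatment maintenance) makes the outcome a two-way label. A sustainer reaches a PASI reduction of 50% or more at 12 weeks and has "maintained this reduction until the end of the follow-up period". A non-sustainer either never reached that reduction or is among "those who did but lost response over the follow-up period and need a change in medication".

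Four other places fix how long each patient is observed:

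- **Entry.** Section 3.2: "It will be included sequentially patients over 18 years of age".
- **End.** Follow up period: "The follow-up period of the study will end in February 2018". Section 3.1 gives the same month: "The deadline for the final analysis of data from the follow-up period will be February 2018".
- **Calendar.** In section 3.1, the row "Data collection and follow up" is marked for 2015 to 2018. No date is given for the end of inclusion. Laboratory analysis is marked for 2017, and section 4.3.3 says "The Elisa will be held only after the end of the inclusion period", so entry could have run into 2017.
- **Visits.** PASI is checked every three months after visit two.

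The Data analysis plan tests the association of "sustainers or non-sustainers status with the categorized variables by the Fisher Exact test", and uses t or Mann-Whitney tests for continuous factors. It names no horizon, minimum follow-up, censoring or adjustment for length of follow-up in these comparisons.

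**The concern.** A label that runs to the end of follow-up has one meaning for all patients only if they are followed equally long. Here the end is a calendar date and the start is each patient's own entry. One week-12 responder may be observed for a few months and another for more than two years, and both receive the same label if no loss has been recorded.

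Three consequences follow. The proportion of sustainers cannot be read as a proportion at any stated time. Differences in follow-up length add misclassification, which weakens real associations in a small study. A factor that tracks entry date can appear related to sustaining response when it is not. Cytokines are the one planned factor for which the protocol itself creates such a link. All ELISA work waits for the end of inclusion, so early entrants have both the longest-stored samples and the longest time at risk. If levels drift in storage, which the protocol does not address, a false association can result.

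**Working it through.** **The plan's own figure.** The protocol gives no figure for the sustainer analysis. Its only sample size, 22 pairs for the PASI comparison (effect size 0.65, 80% power, 5% two-sided), reproduces: a paired t test needs 21 (power 0.809), and 22 gives 0.828. That calculation does not bear on sustainer status.

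**Inputs from the protocol.** Sequential entry, a February 2018 end for all, three-monthly PASI checks, and the two-way label.

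**Assumptions (not in the protocol).** A constant rate of loss after week 12; 10% to 40% loss per year, or a median time to loss of 12 or 24 months; 40% to 70% reaching the 50% reduction at week 12; follow-up after week 12 of about 3 to 30 months.

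**Step 1: chances to record a loss.** With three-monthly checks, 3 months of follow-up gives 3/3 = 1 check and 30 months gives 30/3 = 10.

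**Step 2: week-12 responders, time t from week 12.** P(still sustaining) = exp(−ln 2 × t / median).

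| Assumed median | 6 months | 12 months | 24 months |
| --- | --- | --- | --- |
| 12 months | 0.71 | 0.50 | 0.25 |
| 24 months | 0.84 | 0.71 | 0.50 |

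**Step 3: all patients.** Patients without week-12 response are non-sustainers whatever their follow-up, so P(sustainer) = P(week-12 response) × (1 − annual loss)^(t/12).

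- 60% response, 20% annual loss: 0.57 at 3 months, 0.48 at 12, 0.38 at 24 and 0.34 at 30.
- Smallest gap between 3 and 30 months (40% response, 10% loss): 0.390 − 0.307 = 0.083, or 8 percentage points.
- Largest gap (70% response, 40% loss): 0.616 − 0.195 = 0.421, or 42 points.

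**Step 4: false associations.** The unadjusted t test was simulated for a factor with no effect on loss: 22 patients, 70% week-12 response, follow-up uniform over 3 to 30 months, annual loss of 20%, 30% or 40%, and 6,000 runs per setting. The Monte Carlo standard error is about √(0.05 × 0.95 / 6000) = 0.003.

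| Correlation of factor with follow-up length | Type I error |
| --- | --- |
| 0 | 4.9% to 5.5% |
| 0.3 | 5.7% to 6.0% |
| 0.5 | 6.6% to 8.8% |

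The error rate stays near its nominal value unless the factor is related to entry date, and the inflation is modest even at a correlation of 0.5.

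**The case against.** The strongest reply is that this is a secondary, exploratory objective and that most tested factors (sex, age, disease duration, smoking, alcohol, BMI) have no documented link to entry date. One hospital and one set of criteria apply throughout. This stands. For those factors the harm is misclassification and dilution, not false positives.

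A reader might infer more than the documents support:

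- **That anything related to enrolment date will show a false association.** It can, but the simulated inflation is modest. Shifts in case mix or referral are conjecture. Only storage time has a basis in the protocol, and no storage effect is given.
- **That the Step 2 probabilities apply to every patient.** They hold only for week-12 responders, with time from week 12. With an assumed 60% response, the 12-month-median row becomes 0.60 × 0.71, 0.50 and 0.25, or about 0.42, 0.30 and 0.15 for all patients.
- **That after-treatment markers are measured at the visit that decides non-response, so their associations are invalid.** This is inexact for ESR and CRP, which belong to the three-month tests before visit two. Cytokines are drawn at visit two, but the objective claims association, not prediction. Reporting week-12 response separately would leave them concurrent with it.
- **That pooling week-12 non-response with later loss is an error in itself.** It is a recognisable composite of treatment failure. The problem is that its second part has no fixed duration. How patients lost to follow-up are classified may be settled in a SAP that is not shown.

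A last objection is that a time-to-event analysis would have very few events. This also stands, and the cost is set out with the fix.

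**Conclusion.** The point holds. Sequential entry, one calendar cut-off, an open-ended two-way label and tests that ignore time together make sustainer status depend on entry date among week-12 responders. The direction follows from the protocol alone for any positive rate of loss. The size does not. Under the assumed ranges, the chance of being labelled a sustainer differs by 8 to 42 percentage points between 3 and 30 months of follow-up. Actual entry dates and loss rates are not stated, and a two-year spread in entry is possible but not certain. The analysis should be changed, but the matter is confined to a secondary objective.

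**What to change.** 1. Report week-12 response (PASI reduction of at least 50%) as a separate outcome with the tests already planned.
2. Among week-12 responders, analyse time from week 12 to the first recorded loss of response as the protocol defines it, censored at the last visit or February 2018. Use Kaplan-Meier curves with log-rank tests or single-covariate Cox models, and note that loss is known only to within a three-month visit interval.
3. If a two-way status is preferred, fix one horizon in advance and limit the analysis to patients with that much potential follow-up. At 12 months after week 12, the chance that a responder still sustains is 0.90, 0.80, 0.70 or 0.60 for an assumed annual loss of 10%, 20%, 30% or 40%, whatever the entry date.
4. Record the date of each PASI assessment. The form in Appendix 5 has no date field; the laboratory record in Appendix 4 has one, so past dates may need linkage.

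**Cost.** No extra visits are needed; the change is to analysis wording and one form field. The main downside is few events. Of 22 patients, 40% to 70% gives about 9 to 15 responders. At a mean follow-up of (3 + 30)/2 = 16.5 months, an annual loss of 10% to 20% gives roughly 9 × (1 − 0.9^1.375) = 1 to 15 × (1 − 0.8^1.375) = 4 events. A 12-month median gives about 6 to 9. Results are therefore exploratory, with one covariate at a time. A fixed horizon short enough for every patient could be only about three months, when few losses would be seen; a longer one drops the late entrants.
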